## Abstract

**Background:**

Paranoia (unfounded concerns that other people are deliberately trying to harm you) can be a distressing experience that impacts day-to-day functioning for many people. Digitally delivered interventions are a promising mode of treatment that can increase access to support and reach populations underserved by current provision. One such intervention is the Successful Treatment of Paranoia (STOP) intervention, which is a transdiagnostic self-administered smartphone app for paranoia that was evaluated in England for efficacy in a large, multisite randomized controlled trial. Although there is growing evidence regarding how STOP may work, little is known about the factors that influence its implementation during or after a trial. Understanding these factors is critical for supporting the future adoption of STOP and may inform the implementation of other digital mental health interventions.

**Objective:**

This paper aims to describe the protocol for a process evaluation that will explore intervention implementation to understand how much, by whom, and under what circumstances STOP was used in a trial context and what factors might influence future implementation in routine practice.

**Methods:**

We will conduct a mixed methods process evaluation informed by guidance published by the Medical Research Council in the United Kingdom and embedded in the main STOP efficacy randomized controlled trial, with the aim of understanding who agreed to try STOP, how they used STOP, and users’ and health care professionals’ views on factors that will affect future implementation, including barriers and facilitators. Process evaluation participants will include three samples: (1) STOP trial participants (randomized participants and nonrandomized referrals who agreed to try STOP), (2) individuals experiencing paranoia who participated in the Adult Psychiatric Morbidity Survey in England, and (3) health care professionals in England. We will use mixed methods data collected in the STOP trial (demographics, app use, recruitment data, and qualitative data exploring intervention acceptability from the perspectives of users and health care professionals) and demographic data from another paranoia population collected in the Adult Psychiatric Morbidity Survey.

**Results:**

The STOP trial was completed in December 2024, having recruited 274 participants. The process evaluation received funding in winter 2023. As of December 2025, data analysis for process evaluation studies 2 and 3 is ongoing following preregistration in July 2025. Results are expected to be completed and submitted for publication by February 2027.

**Conclusions:**

Findings from this process evaluation will help develop an evidence-based understanding of implementing STOP, including identifying suitable implementation strategies for posttrial delivery both inside and outside mental health services. Our findings will inform future iterations and the upscaling of STOP and may inform implementation of other self-administered digital mental health interventions.

**Trial Registration:**

International Standard Registered Clinical/Social Study Number ISRCTN17754650; https://www.isrctn.com/ISRCTN17754650

**International Registered Report Identifier (IRRID):**

DERR1-10.2196/81167

## Introduction

### Background

Paranoia refers to concerns that others may intend to harm you [1,2]. Freeman’s [1] theoretical model of paranoia suggests a hierarchy, whereby more severe forms of paranoid worries in clinical populations (eg, believing others are trying to kill you) build on milder, everyday forms of social evaluative concerns (eg, believing others are talking about you behind your back), which are commonly experienced in the general population. Paranoia is often a distressing experience that can negatively interfere with many aspects of life, including people’s everyday activities [3] and interpersonal relationships [4]. Many people can experience paranoia, including those with psychosis spectrum disorders, but it is also a transdiagnostic symptom and can be present in other mental health conditions as well, including depression and anxiety disorders [5]. Paranoia can also be experienced by nonclinical populations across the lifespan [3,6].

To improve the lives of those experiencing paranoia, developing support (eg, to reduce paranoia or sustain recovery) for this population has been identified as a research priority by patients, carers, researchers, and health care professionals in an international priority setting partnership [7]. One promising treatment mode for those experiencing paranoia is digital mental health interventions (DMHIs), or treatment that incorporates technology to improve users’ mental health [8]. An early value assessment conducted by the National Institute for Health and Care Excellence identified specific DMHIs as suitable for full recommendation, subject to further data collection [9]. Early recommendation of this sort can improve the provision of care by increasing treatment options and access to support using fewer resources than in-person treatments [9]. Preliminary evidence suggests that DMHIs may be an acceptable and feasible treatment for paranoia [10].

### What Is Successful Treatment of Paranoia?

While other DMHIs for paranoia have been developed, most are delivered via virtual reality, require clinical support, or focus on other psychotic experiences (eg, voices) and pay limited attention to more common, social evaluative concerns within paranoia (eg, that others are talking about you negatively) [10]. Successful Treatment of Paranoia (STOP) was developed to address these limitations by providing a self-delivered, smartphone-based transdiagnostic intervention specifically targeting interpretation biases underpinning paranoia. The intervention and its development have been described in detail elsewhere [11,12]. A brief description is included to contextualize our work.

STOP is a self-administered psychological intervention using the principles of cognitive bias modification for paranoia (CBM-pa). CBM-pa aims to address the cognitive interpretation bias that is thought to cause and maintain the symptoms of paranoia [13]. Individuals displaying this interpretation bias often interpret neutral or ambiguous social scenarios as personally threatening [13]. There is preliminary evidence from a feasibility randomized controlled trial (RCT) that interpretation biases can be modified by CBM-pa that was delivered via a desktop computer in a research laboratory setting (N=63) [14].

STOP in the RCT included a weekly session administered through a smartphone app either on users’ personal smartphones or, if needed to avoid digital exclusion, on a study phone with a data plan provided free of charge to participants. Two versions of the intervention of varying lengths were evaluated to investigate “dose” effects (6 vs 12 weeks). Users scheduled weekly sessions at convenient times, during which they read 40 everyday social scenarios. In the sessions, users were encouraged to interpret ambiguous social scenarios in a nonthreatening way by completing a word puzzle and then answering a question about the meaning of the scenario (Figure 1 includes an intervention example). Session content was designed by clinicians, academics, and the McPin Foundation research charity’s STOP lived experience advisory panel (LEAP) of 7 people who give voice to intended end users of the app to increase its clinical relevance and acceptability to users [11]. Automated phone and email reminders were sent at midnight 1 day before the scheduled session and again if a session was not completed on the scheduled day.

**Figure 1 figure1:**
[figure not shown]
Successful Treatment of Paranoia (STOP) intervention example.

### How Do We Think STOP Will Work?

Program theories underpin interventions and explain how, why, for whom, and in which circumstances interventions are assumed to work and can be represented visually in a logic model [15]. A logic model for the STOP intervention was created after conducting a document analysis of the trial protocol and publications associated with the intervention (Figure 2) [11,12]. An initial program theory was developed from the logic model (Textbox 1).

**Figure 2 figure2:**
[figure not shown]
Logic model for the Successful Treatment of Paranoia (STOP) intervention.

Program theory for the Successful Treatment of Paranoia (STOP) intervention.Users complete cognitive bias modification for paranoia (CBM-pa) training items delivered via a smartphone app, which creates a cognitive change that enables the user to consider a more neutral interpretation of ambiguous situations.The cognitive change has a positive impact on users’ mental health and recovery, including reducing symptoms of paranoia.

### Why Conduct a Process Evaluation?

We will conduct a process evaluation to better understand the factors influencing DMHI implementation both during and after the trial. Exploring factors that may influence implementation is an important research focus as the implementation of DMHIs is a persistent challenge [16,17], and it is also acknowledged that interventions may be used differently across settings and populations [18,19]. There is some empirical evidence for this as reviews have demonstrated DMHI use can vary due to several factors, including patient characteristics (eg, age) and intervention features (eg, including human support) [20]. However, implementation remains a key area of uncertainty in the STOP trial as it is currently unknown what, or if any, factors influence the implementation of STOP (Figure 2, context box). A limited understanding of implementing STOP contrasts with a comparatively better understanding of how STOP is assumed to work, for which there is a growing evidence base [13,14] and plans to evaluate mechanisms of action in other trial work [12]. Intervention implementation is an important uncertainty to address given that STOP has the potential to be implemented in a variety of settings (as users choose where and when sessions are accessed) and by a variety of potential end users (as users may not need to be under the care of a health service or have a formal mental health diagnosis to use STOP) [12].

### Evaluation Objectives

Our work aims to address these knowledge gaps by exploring the factors that influence the implementation of a self-administered digital intervention for paranoia in and after an RCT. The overarching objective of this evaluation is to develop an evidence-based understanding of implementing STOP by investigating how much, by whom, and under what circumstances STOP is and may be implemented in and after a trial. A secondary objective is to use this knowledge to identify the barriers and facilitators to implementing STOP in and after a trial.

## Methods

### Overview

We will conduct a mixed methods process evaluation of STOP. The protocol is reported using an amended version of the process evaluation recommendations from the Medical Research Council (MRC) process evaluation framework (Table S1 in Multimedia Appendix 1) [18]. We amended the reporting standards to fit the reporting of a protocol paper by removing sections that are not applicable (ie, those relating to reporting evaluation findings). Details of the core research team (CH, CD, JY, and PJ) are provided in Multimedia Appendix 2.

### Ethical Considerations

The STOP trial was preregistered at ISRCTN (ISRCTN17754650) and approved by the London-Stanmore Research Ethics Committee (21/LO/0896, January 14, 2022) and the Medicines and Healthcare products Regulatory Agency (CI/2022/0033/GB, July 19, 2022), including approval for collecting additional qualitative data with STOP users and health care professionals. An additional qualitative study involving STOP trial participants was conducted and approved separately by the University of Bath Social Sciences Research Ethics Committee (0179-353). Written informed consent was obtained from all participants prior to data collection, with the option to withdraw at any time without specifying a reason. Participants were compensated for their time: trial participants received up to £115 (US $153; £20 [US $26.6] per follow-up assessment, an additional £20 [US $26.6] at the trial end, and £15 [US $19.95] after completing an additional interview), health care professionals received a £20 (US $26.6) voucher, and nonrandomized STOP users received £40 (US $53.2). All participants were assigned unique study identifiers, and only fully anonymized and deidentified data will be accessed for analyses. The process evaluation was approved by the University of Bath Social Sciences Research Ethics Committee as a requirement of the doctorate (5841-6196). Further ethics approval was not required because the process evaluation did not introduce additional trial procedures or data collection and will only use existing data from participants who consented to data archiving.

### Process Evaluation Design

We will use the 2015 MRC process evaluation guidance as a methodological framework, which assumes that an efficacy evaluation in isolation provides a limited understanding of an intervention [18]. Instead of evaluating intervention efficacy, process evaluation in the MRC framework explores 3 proximal outcomes which can complement efficacy evaluations (Textbox 2) [18].

Medical Research Council (MRC) process evaluation components.Context: external factors that influence intervention functioning or delivery.Implementation: intervention delivery in the evaluation.Mechanisms of impact: how interventions produce change.

### How is STOP Being Evaluated?

#### Efficacy RCT

The process evaluation is embedded within the host RCT evaluating the efficacy and safety of STOP compared with an active control condition (a 12-week text reading control delivered through the STOP app, where users read and responded to items, including facts or unambiguous everyday experiences without a social component, such as making a cup of coffee) [12]. The RCT was preregistered (ISRCTN17754650), and a detailed protocol has been published [12]. The RCT was run by 2 main recruitment coordinating hubs at King’s College London and the University of Bath in England [12]. Recruitment in the RCT ran from September 2022 to June 2024, closing after 274 participants were randomized, and data collection was completed in December 2024. Participants were recruited from 3 main sources, including 20 National Health Service (NHS) trusts, third sector organizations coordinated by the McPin Foundation, and via self-referral routes using recruitment posters or the study website [12]. Individuals aged 18 years or older who were experiencing mild to moderate-severe paranoia (operationalized as a score between 3 and 6 out of 7 on item 6 on the Positive and Negative Syndrome Scale [21] during screening) and displaying an interpretation bias toward paranoid meanings (operationalized as a score between −2 to +3 on a scale ranging from −3 to +3 the Similarity Rating Task during screening) were eligible for the RCT [12]. Individuals who were at high risk of suicide, lacked the capacity to consent, or could not communicate in written or spoken English were excluded from the RCT [12].

#### Planned Process Evaluation Studies

We will conduct 3 studies that will explore the implementation of STOP. The data sources and research questions per study are summarized in Figure 3. Study methods and progress are reported for each of the planned studies in further detail below. The process evaluation is preregistered on the Open Science Framework [22].

**Figure 3 figure3:**
[figure not shown]
Overview of Successful Treatment of Paranoia (STOP) process evaluation questions and methods. RCT: randomized controlled trial.

#### Study 1: Exploring the Uptake of STOP in an RCT

### Overview

This mixed methods study will conduct analyses on STOP trial routine data and secondary analyses on sociodemographic data from another paranoia population in England.

### Aim

To summarize who agreed to take part and try STOP in a trial (STOP uptake), to describe factors that influenced uptake, and to characterize and assess the representativeness of those agreeing to try STOP compared with another paranoia population in England.

### Participants and Recruitment

STOP RCT participants and recruitment procedures are described earlier (in the Efficacy RCT section) and in full in the protocol paper [12].

### Measures

Measures will include intervention uptake, factors influencing uptake, and the characteristics of individuals who agreed to try STOP compared with a paranoia population in England. Intervention uptake will be summarized using trial records to report the number and percentage of those agreeing to try STOP out of those who were approached to take part in the trial at different time points in the RCT (eg, consent, screening, and randomization) to summarize the uptake of STOP in a trial.

Factors influencing uptake will be identified from qualitative reasons reported by those agreeing to and declining to try STOP at different time points in the RCT (eg, consent, screening, and randomization), using STOP trial documents (eg, CONSORT diagrams, STOP case report forms, and recruitment trackers) to describe factors that facilitated or hindered the uptake of STOP in a trial.

Characteristics of those agreeing to try STOP compared with a paranoia population in England will be assessed using sociodemographic data obtained from STOP trial baseline data and from the Adult Psychiatric Morbidity Survey (AMPS) conducted in 2023 to 2024 by Public Health England, which provides data about treated and untreated psychiatric disorders among adults in England [23], to characterize and assess the representativeness of those agreeing to try STOP. We will compare those who agreed to try STOP with the subsample of responders endorsing items indicating paranoid thinking, which is a method that has been adopted in other analyses of AMPS [24,25]. We are unable to prespecify the variables or which items and measures will be used to indicate paranoia because data from the AMPS are not available at the time of publication [23]. However, based on the most recently available AMPS dataset published in 2016 [26], probable variables include age, sex, ethnicity, living arrangement, region, employment status, and current treatment.

### Analysis

Rates of uptake will be summarized descriptively. Qualitative data from STOP trial documents will be analyzed in the latest version of NVivo (Lumivero) to provide an audit trail using a framework analysis approach [27,28], and findings from all trial documents will be triangulated. We will use the Consolidated Framework for Implementation Research (CFIR) [29] as a deductive framework to identify factors influencing uptake. Data that cannot be coded using a priori codes from the framework will be inductively coded in an “other” category. Qualitative analysis will be led by CH, but codes and themes will be developed and reviewed by the core research team (CD, JY, and PJ). STOP trial participants will be characterized using descriptive statistics from the trial’s main outcome paper, supplemented as necessary by further information. Exploratory quantitative analyses will be conducted using relevant packages in the most recent version of R software (R Foundation for Statistical Computing) to test for between-group differences using chi-square tests and 2-tailed *t* tests where appropriate. If necessary, a *P* value correction will be used to account for multiple testing.

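### Study 1 sets out to assess representativeness, but the only comparison it names is difference testing, whose P values do not measure it

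*Protocol article*

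**What the plan says.** The Aim of Study 1 includes the intention to "assess the representativeness of those agreeing to try STOP compared with another paranoia population in England". The Measures section identifies the comparator: "We will compare those who agreed to try STOP with the subsample of responders endorsing items indicating paranoid thinking". It lists seven probable variables (age, sex, ethnicity, living arrangement, region, employment status, current treatment). It also says openly that the choice is not final: "We are unable to prespecify the variables or which items and measures will be used to indicate paranoia", because the survey data were not yet available.

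The Analysis section gives the method. STOP participants are characterised with descriptive statistics. Then "Exploratory quantitative analyses will be conducted using relevant packages in the most recent version of R software", and their purpose is "to test for between-group differences using chi-square tests" and two-tailed t tests where appropriate. If needed, a P "value correction will be used to account for multiple testing". No difference measure, confidence interval or tolerance is named for the comparison with the survey. Survey weights and design variables are not mentioned either way.

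The Efficacy RCT section describes who could enter the trial: adults with a score of 3 to 6 on one item of the Positive and Negative Syndrome Scale and an interpretation-bias score in a set range. It adds: "Individuals who were at high risk of suicide, lacked the capacity to consent, or could not communicate in written or spoken English were excluded". No corresponding restriction is stated for the survey subsample.

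**The concern.** Representativeness is a question of size: how far do the people STOP reached differ from people with paranoia in England, and on which characteristics? A difference test answers another question, namely whether the data are compatible with no difference at all. Its result depends on the number of survey respondents as much as on the gap. With a small subsample a sizeable gap can go undetected, and with a large one a minor gap is declared significant.

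Two features of the comparison add to this. First, if the survey has a complex design and weights, a plain test that ignored them would misstate the uncertainty and could misstate the survey percentages. Second, the STOP side has passed through eligibility rules that the survey side has not. A gap in ethnicity or current treatment, for example, may come from who was allowed in as well as from who agreed.

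The findings are meant to feed a framework for delivering STOP inside and outside mental health services. A mistaken conclusion about whom STOP reaches would carry into that framework.

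**Working it through.** The article states no survey subsample size, power, alpha or margin for Study 1, so there is no figure of its own to reproduce. What follows is an illustration.

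**Inputs**
- STOP side: n = 274 randomized (Efficacy RCT section). The Abstract also counts nonrandomized referrals who agreed to try STOP, without giving their number, so 274 is itself a working value.
- Survey side: m = 100 to 1000 (assumption).
- Two-sided alpha 5%, power 80% (assumptions); multiplier 1.96 + 0.84 = 2.80.
- Prevalence p = 50% or 20% (assumption).

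**Detectable gap.** Formula: 2.80 × √[p(1−p)(1/274 + 1/m)].
- p = 50%, m = 100: 2.80 × √(0.25 × 0.01365) = 2.80 × 0.0584 = 16.4 points.
- p = 50%, m = 1000: 2.80 × √(0.25 × 0.00465) = 2.80 × 0.0341 = 9.5 points.
- p = 20%: 13.1 points at m = 100 and 7.6 points at m = 1000.
- For a mean, such as age, in standard deviation units: 2.80 × √(1/274 + 1/m) = 0.33 at m = 100 and 0.19 at m = 1000.

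A calculation that uses the variance at each of the two proportions gives 16.1 points at m = 100. By the same calculation, a true gap of 10 points near 50% is detected with 40% power at m = 100 and 58% at m = 200.

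**The same gap with different P values.** Suppose the observed gap is 8 points near 50%, a standardised difference of 0.08/0.5 = 0.16.

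| m | SE (points) | z | P | 95% CI (points) |
|---|---|---|---|---|
| 100 | 5.84 | 1.37 | 0.17 | −3.4 to 19.4 |
| 1000 | 3.41 | 2.35 | 0.019 | 1.3 to 14.7 |

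The test result changes and the gap does not. The interval shows at once what each subsample can and cannot exclude. At m = 1000 any observed gap above 1.96 × 3.41 = 6.7 points is significant, whether or not it matters.

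**Survey design, if it were ignored.** With design effect D on the survey side (assumed 1.3 to 2.0), the true type I error of a nominal 5% test is 2 × [1 − Φ(1.96 × √{(1/274 + 1/m)/(1/274 + D/m)})].
- m = 100: 7.6% (D = 1.3) to 13.6% (D = 2.0).
- m = 1000: 5.7% to 7.5%.

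These figures apply only if weights and design variables exist and are not used. The article says neither.

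**The case against.** The strongest reply is that this is an article, that it defers detail openly, and that the deferral is reasonable. The variables and the paranoia items wait for the survey data, the Strengths and Limitations section promises analysis plans on the Open Science Framework before analyses start, and the tests are labelled exploratory. That stands for the variables and the items. It does not reach the point made here. Choosing a measure of difference needs no survey data, and the Analysis section has already named the method of comparison. The descriptive statistics it mentions are for the trial participants and are not a measure of the gap between the two groups.

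A reader might infer three stronger things that the document does not support:
- *That the survey will be analysed unweighted.* The article is silent. Unspecified R packages could include design-based versions of these tests, and the article does not describe the survey's sampling design.
- *That the survey subsample ought to be cut down to match trial eligibility.* The stated aim is comparison with another paranoia population, and the survey is described as covering treated and untreated disorders. How far STOP participants differ from that wider group, eligibility rules included, is a legitimate question. A restricted main comparison would answer a different one and remove part of the gap the study wants to describe.
- *That a non-significant P value will be declared proof of representativeness.* No such decision rule is written. The article leaves that reading open and offers no better measure.

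It is also fair to say that the sizes above rest on assumed survey numbers, and that the 13.6% pairs the smallest subsample with the largest design effect.

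**Conclusion.** The point holds in a limited form. The aim is representativeness, and the only comparative method named is a set of exploratory difference tests that do not measure it. The logic does not depend on the survey's size; the figures do. With 274 participants and an assumed 100 to 1000 survey respondents, 80% power is reached only for gaps of about 16.4 down to 9.5 points at 50% prevalence, so a non-significant result is compatible with gaps that would matter for access.

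That no weighting or design adjustment is stated is something to settle in the plan, not evidence that it will be omitted. The lack of eligibility alignment is a matter of interpretation, not a fault in the comparator. No figure in the article is wrong on this point. Study 1 analysis is reported as not yet started and is scheduled for spring 2026, so the change can be made in the promised analysis plan.

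**What to change.** In the Study 1 Analysis section, or in the Open Science Framework plan that carries it:

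1. Define the measure of representativeness as the difference between STOP participants and the survey paranoia subsample. Report it for each variable as a standardised difference and as a difference in percentages or means with a 95% confidence interval. Keep P values as secondary.
2. Estimate the survey side with the survey's weights and design variables if they are supplied, and say so. If they are not supplied, state that as a limitation.
3. Keep the broad paranoia subsample as the main comparison. State that differences reflect trial eligibility and uptake together.
4. Optionally, add a sensitivity comparison with a survey subsample aligned to trial eligibility where the survey items allow it.

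The cost is some analysis-plan wording, a little more analysis work and wider intervals. At 50% prevalence the half-width is 1.96 × √[0.25(1/274 + D/m)]. At m = 1000 it rises from 6.7 points to between 6.9 (D = 1.3) and 7.4 (D = 2.0). At m = 100 it rises from 11.4 to between 12.6 and 15.1. The widening is slight unless the subsample is small and the design effect large. No new data collection is needed.
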